### **Stool sample analysis**

The study participants will collect the stool samples by using specific collection tubes at three consecutive time points: before administration of metformin, on the day when the treatment is started (after the first dose) and after a week-long metformin treatment. During the

regular visits, the investigator or his representative will advise the participants about an optimal time for collecting stool samples. Participants will deliver the samples to LBMC during their regular visits. Samples will be collected in two aliquots, one of them will be used for the isolation of microbial DNA and subsequent metagenome and metabolite analysis, the second aliquot will be stored as a backup sample at -70 ° C in the BMC premises.

The microbial DNA will be isolated from the stool samples and further used to determine the taxonomic alterations in the composition of gut microbiome according to the 16S rRNA gene fragment sequences obtained. In addition, shotgun metagenome sequencing will be performed, providing the information about the metabolic processes and function of the gut microbiome. The alterations in the composition of gut microbiome induced by metformin will be evaluated by comparing the microbial composition of stool samples collected before the first intake of metformin and during or after administration of metformin.

**Methods:** Microbial DNA from fecal samples will be isolated using FastDNA kit for Soil (MP Biomedicals), following the manufacturer's instructions. The 16S rRNA gene fragment analysis and shotgun metagenomic sequencing (Ion Plus Fragment Library Kit, Thermo Fisher Scientific) will be performed on a large-scale parallel sequencing platform (Ion Torrent). A detailed analysis of the individual taxonomic groups of bacteria will be carried out using the Sanger sequencing method and real-time PCR. Determination of metformin and various metabolites in samples (blood and stool) will be carried out with MALDI-TOF mass spectrometers and equipment available in the Latvian Institute of Organic Synthesis (OSI): gas chromatography (FID, ECD, TCD, MSD) and liquid chromatography - tandem mass spectrometry (LC-MS / MS).

The technical equipment needed to conduct the sample analysis in LBMC: automatic pipetting, PCR devices, real-time PCR devices (7500 and ViiTM7), sequencing analysis system 3130 XL, IonTorrent PGM and IonProton sequencer, MP FastPrep based on large-scale parallel sequencing technology 24 disintegrators, ultrasonic disintegration system "Covaris S220 AFA", Qubit® 2.0 fluorometer and Agilent 2100 bioanalyzer for measuring DNA quality.

## Questionnaires

During the second visit the study participants will receive a diet diary and a general questionnaire. The general questionnaire includes questions related to the participant's health status and nutrition. The information gathered will be further used to identify additional factors influencing the composition of gut microbiome and epigenetic profiles. General information on health and heredity will be collected as a routine procedure in LGDB. The diet diary contains clear instructions for accurate description of the daily diet and assessment of the level of physical activity during the study. The diet diary will be provided in both printed and electronic forms. At the end of the study participants will be asked to fill the questionnaire on side effects, assessing the feeling of well-being during the study period and documenting the side effects observed. Participants will be requested to immediately inform the organizers in case of using

other medications during the trial period, in order to identify the health conditions unrelated to metformin.

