### 3. Observational period

After a seven-day use of *Metforal* 850 mg, the participants will fill out the questionnaire on the observed side effects assessing the feeling of well-being during the study. The day after the last dose of *Metforal* 850 mg, the last blood and fecal sample will be collected.

Participants will be involved in the study for a duration of 13 days. Within the framework of the study seven visits to the investigator and one phone visit will be organized:

***1st visit.*** During the first visit the investigator will introduce the potential study participant with the course of the study, inform about possible risks and benefits and provide the informed consent form. After this visit, each potential participant will get acquainted with the informed consent form and make a decision on participation in the study.

***2nd visit - Study Day 1.*** Volunteers agreed on their participation in the study will submit a signed and dated informed consent form to the investigator. The investigator will evaluate the participants' compliance with the inclusion / exclusion criteria. In case of non-compliance, the reasons for the exclusion of the participant will be documented. During the visit, participants will receive a copy of the informed consent form signed by the participant and the investigator, instructions for stool sample collection, tubes for stool sample collection, diet diary form, general questionnaire, questionnaire on side effects, LGDB health and heredity questionnaire. During the visit, the investigator will carry out the biometric measurements necessary for the completion of LGDB questionnaire. Starting from this day, the participant will be asked to fill out the diet diary in paper or electronic format following the instructions given therein. During the verification period (see Figure 1), the participant will be asked to collect their first stool sample for the gut microbiome analysis, before starting the administration of metformin. The collection and storage of stool samples will be carried out in accordance with the procedure described in the stool sampling protocol. The participant will be asked to find the nearest E. Gulbis laboratory where venous blood samples (11 ml) for hematological and biochemical analysis will be collected. After receiving the results of hematological and biochemical analysis the investigator will evaluate the compliance of the study participant again.

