### **Endpoints of the study**

The primary endpoint of the study is a significant change in the composition of the gut microbiome in healthy subjects (composition and proportion of taxonomic units) after administration of metformin.

Secondary endpoints of the study:

- 1) Significant alterations in DNA methylation profiles and RNA expression levels in healthy subjects following metformin use;
- 2) Association of DNA methylation profiles with severity of adverse reactions.
- 3) Association of specific gut microbial taxonomic units with severity of adverse reactions;
- 4) The association of specific taxonomic units with changes in the metabolite profile in the blood / faeces.
- 5) Association of pharmacokinetic parameters with specific taxonomic units of gut microbiome and changes in DNA methylation and gene expression profiles.

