### **SAFETY CONSIDERATIONS**

The research safety assessment will be carried out during each visit based on the information provided by participant on their well-being and health status since the beginning of *Metforal* 850 mg administration or previous visits. All participants of the study will be advised to inform the research organizers by telephone on any arisen health risks also outside the time of visits, if necessary. During the study all the side effects observed will be documented in detail in a specific questionnaire, indicating the type of side effects observed, time, and frequency of recurrence. Approximately 72 hours after the last dose of *Metforal* 850 mg the investigator will survey on phone all participants involved in the study in order to obtain more

information and evaluate their state of health and, if necessary, recommend visiting physician or certified specialist.

If any of the study participants is harmed as a result of the clinical trial, the compensation will be paid in accordance with the sponsor's concluded insurance contract. Visits to the physician, in case of side effects or adverse events will be compensated after the submission of payment document and a physician's conclusion that the cause of observed side effects is metformin therapy.

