### **AE classification by severity:**

***Mild*** - Awareness of signs or symptoms, but easily tolerated and are of minor irritant type causing no loss of time from normal activities. Symptoms do not require therapy or a medical evaluation; signs and symptoms are transient.

***Moderate*** - Events that introduce a low level of inconvenience or concern to the participant and may interfere with daily activities, but are usually improved by simple therapeutic measures; moderate experiences may cause some interference with functioning

***Severe*** - Events that interrupt the participant's normal daily activities and generally require systemic drug therapy or other treatment; they are usually incapacitating

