### **Assessment and reporting of adverse reactions**

The adverse reactions observed will be documented by the participant at the end of the active period of the study by using a specific questionnaire on side effects. The investigator will immediately inform the sponsor of any serious adverse event related to the subjects involved in the clinical trial. The sponsor will ensure that all undesirable events reported by the investigator or his research team are documented. At the end of the active period of the study the investigator does not apply monitoring of undesirable events to subjects involved in the clinical trial. If the

investigator receives information about serious adverse events after the trial is completed, the investigator will report it to the sponsor.

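### The protocol describes no pre-dose gut-symptom measure and does not tie its severity scale to the side-effect form, so background symptoms may enter the secondary tolerance endpoints

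*Protocol*

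**What the plan says.** **When the form is filled.** The participant receives it on Day 1 (2nd visit) and returns it on Day 12 (7th visit). Completion is placed after treatment in several sections:
- Questionnaires: "At the end of the study participants will be asked to fill the questionnaire on side effects".
- Observational period: after seven days of drug, "the participants will fill out the questionnaire on the observed side effects assessing the feeling of well-being during the study".
- Assessment and reporting of adverse reactions: the reactions "will be documented by the participant at the end of the active period of the study by using a specific questionnaire on side effects".
- Potential benefits and risk factors: also at the end of the study.
- Figure 1: general questionnaires in the verification period, side-effect questionnaires in the observational period.

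**What it contains.** Safety considerations describes it as "indicating the type of side effects observed, time, and frequency of recurrence". Severity is not in that list.

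**What the endpoints need.** Secondary endpoint 3 is "Association of specific gut microbial taxonomic units with severity of adverse reactions", and secondary endpoint 2 does the same for DNA methylation. The statistical methodology section plans a chi-squared test for taxa against severity and an ANOVA for methylation against severity.

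**Where severity is defined.** AE classification by severity gives three grades, the lowest beginning "Awareness of signs or symptoms, but easily tolerated". It names no rater and no time of grading, and does not mention the form or the endpoints.

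**The concern.** The Study design section rests the trial on each participant being their own control. Microbiome, methylation, RNA and metabolites all have a pre-dose sample. Tolerance, the variable those profiles are to be related to, has no stated pre-dose counterpart.

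Someone with recurrent indigestion or nausea may report it on Days 4–10 whether or not metformin caused it. Participants will also have been told before dosing which side effects to expect, and the form asks them to look back over the whole period. If background symptoms are unrelated to the gut flora, mixing them in dilutes a real association. If they are related to it, an association could appear that reflects pre-existing gut symptoms and not response to the drug. What is at stake is secondary objective 1 and secondary endpoints 2 and 3.

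This is not something to leave to an analysis plan. A plan can define a tolerance variable, but it cannot recover symptoms that were not collected before dosing.

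**Working it through.** **1. Is there a figure in the plan to reproduce?** Not for this point. The sample size of 50 (80% power, alpha 0.05, about 2% loss) comes with no effect size or tested variable. Only the loss step can be checked: 49 / 0.98 = 50. Nothing below depends on it except the use of 49 completers in step 4.

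**2. Pre-dose information the protocol does describe.**

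| Source | Covers | Gives a gut-symptom baseline? |
|---|---|---|
| Exclusion criteria | Chronic intestinal disease, diarrhoea in the past week, proton pump inhibitors in the previous two months | Removes some cases; occasional indigestion, nausea or abdominal pain is not named |
| General questionnaire | Health status and nutrition | Symptom items not stated; form not shown |
| Safety assessment at visits | Well-being since metformin began or since the previous visit | Not linked to the tolerance endpoints |
| Side-effect form | Type, time, frequency | Completed after dosing |

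No section compares symptoms before dosing with symptoms on the drug.

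**3. Illustrative size of the mixing.** Let d be the drug-induced rate and b the background rate, taken as independent. The Rationale section gives gastrointestinal side effects in 10–20% of metformin users, used here for d. The protocol gives no background rate, so b = 5–30% is an assumption.

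Share of reporters with background symptoms only = b(1 − d) / [1 − (1 − b)(1 − d)]

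- b = 0.15, d = 0.15: 0.1275 / 0.2775 = 0.46. Of 50 participants, 50 × 0.2775 = 13.9 report symptoms, and 50 × 0.1275 = 6.4 of them have background symptoms only.
- Lowest: b = 0.05, d = 0.20: 0.04 / 0.24 = 0.17.
- Highest: b = 0.30, d = 0.10: 0.27 / 0.37 = 0.73.

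If background symptoms are unrelated to the taxon, the reporter versus non-reporter contrast shrinks by the factor (1 − share). At 46% it is 54% of its true size.

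**4. What that could do to a test.** Further assumptions: 49 completers, and a taxon present in 70% of truly intolerant participants and 30% of the others. Two-sided alpha is 0.05, by normal approximation.

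| d | b | Reporters | Background only | Difference in taxon presence | Power |
|---|---|---|---|---|---|
| 10% | 0% | 4.9 | 0% | 40 points | 42% |
| 10% | 5% | 7.1 | 31% | 28 points | 31% |
| 10% | 10% | 9.3 | 47% | 21 points | 24% |
| 10% | 20% | 13.7 | 64% | 14 points | 16% |
| 20% | 0% | 9.8 | 0% | 40 points | 64% |
| 20% | 5% | 11.8 | 17% | 33 points | 54% |
| 20% | 10% | 13.7 | 29% | 29 points | 46% |
| 20% | 20% | 17.6 | 44% | 22 points | 34% |

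The cells are small and the approximation is rough. The table shows that with about 5 to 10 true cases, modest mixing can matter. It does not estimate the loss in this trial.

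**The case against.** A reader might infer that ordinary gut symptoms will be classed as metformin intolerance. The document does not say so. It gives no tolerance variable and no attribution rule, and how severity is derived may be left to an analysis plan that is not shown. What the text supports is that such symptoms may be counted.

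A reader might also infer that the protocol holds no symptom information apart from one retrospective form. That too goes further than the text:
- "The research safety assessment will be carried out during each visit", with a Day 6 control visit and a Day 13 call.
- Safety considerations has side effects documented during the study, with their time. Dosing starts on Day 4, so some can be placed before or after the first dose.
- Healthy status is required and some gut illness is excluded.
- The general questionnaire is reviewed before dosing and is meant to identify other influences on the profiles.
- A severity scale exists, and the rules that refer to moderate or severe reactions presuppose that someone grades them.
- The forms are available on request and unseen here, so a symptom or severity item cannot be ruled out.

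The numbers are open to challenge as well. The background rate is assumed. The 10–20% may already include background symptoms, so adding more could double count. The calculation treats symptoms as yes or no, while the endpoints use severity, and background symptoms graded mild would do less harm. The 54% figure needs background symptoms unrelated to taxa, whereas a spurious association needs the reverse, so both harms cannot be claimed from one calculation.

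All of this stands as a limit on the claim. It does not supply the missing baseline. A recurrent complaint that returns on Days 4–10 carries an on-drug time, and a form about side effects has no stated reason to record a symptom from before the drug. The visit checks and the severity scale are not connected to the endpoints.

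**Conclusion.** The point holds as a gap in data collection. The protocol describes no pre-dose gut-symptom measure, places completion of the side-effect form after treatment, and does not connect its severity scale to the form or to the endpoints that use severity. Background symptoms may therefore be counted as side effects.

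The size in this trial is unknown. The 17–73% share rests on an assumed 5–30% background rate, independence from the drug effect, and a yes/no symptom model. It should be cited only as an illustration.

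The document does not support saying that background symptoms are counted as intolerance, that severity goes unrecorded, or that the primary endpoint is compromised. The study is exploratory and the affected endpoints are secondary. The change is worth making because it is cheap and cannot be made after dosing.

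**What to change.** 1. Have participants complete the same symptom items once before the first dose (Days 1–3, returned at the Day 4 visit with the general questionnaire) and again after treatment (returned on Day 12 as planned).
2. Grade each item on the protocol's existing mild/moderate/severe scale, and say who grades it.
3. Define the tolerance variable in secondary endpoints 2 and 3 as new onset or worsening from the pre-dose record.
4. Reconcile Safety considerations, which has side effects documented during the study, with the sections that place completion of the form at the end.

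One pre-dose record removes persistent symptoms better than intermittent ones, so some mixing will remain. Daily scoring to Day 13 is not needed, and it would not fit the return of the form on Day 12.

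**Cost:** a small protocol amendment, a reprinted form and a few minutes per participant, with no added visit or sample. Asking about symptoms beforehand may prompt more reporting, but it does so at both time points.

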### **Evaluation of efficiency of investigational product**

The metformin-induced effect will be evaluated based on the results of microbial, metabolite, pharmacokinetic, DNA methylation and RNA expression analysis.

#### Primary parameters for efficacy measurements:

1. Alterations in the composition of the gut microbiome of healthy individuals (number of taxonomic units, proportion);
2. Alterations in the functions of gut microbiome in healthy individuals (number of gene families represented, signaling pathways, metabolites and their concentrations);
3. Alterations in DNA methylation and transcriptome profiles (Beta value, fold-change, Spearman correlation coefficient, p-value).

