### **Secondary objectives:**

- 1) Evaluate gut microbiome taxonomic profile in association of metformin tolerance;
- 2) Distinguish the changes in gut microbiome induced by metformin administration from those initiated by diet;
- 3) Evaluate changes in white blood cell RNA expression and DNA methylation profiles;
- 4) Analyze the association between metabolite profile changes in blood/faeces and the gut microbiome composition;
- 5) Determine the effect of metformin pharmacokinetics on gut microbiome composition and DNA methylation profiles.

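### The protocol contradicts itself on which outcomes are primary: three families under the efficacy parameters, one under the endpoints, and change in microbiome function missing from the endpoints altogether

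*Protocol*

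**What the plan says.** The Protocol ranks its outcomes in more than one place.

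- **Primary parameters for efficacy measurements** has three items: "Alterations in the composition of the gut microbiome of healthy individuals (number of taxonomic units, proportion"; "Alterations in the functions of gut microbiome in healthy individuals (number of gene families represented, signaling pathways, metabolites and their concentrations"; and "Alterations in DNA methylation and transcriptome profiles (Beta value, fold-change, Spearman correlation coefficient, p-value".
- **Endpoints of the study** has one primary endpoint: "The primary endpoint of the study is a significant change in the composition of the gut microbiome in healthy subjects". The first secondary endpoint is "Significant alterations in DNA methylation profiles and RNA expression levels in healthy subjects following metformin use". The nearest entry to microbiome function is the fourth secondary endpoint, "The association of specific taxonomic units with changes in the metabolite profile in the blood / faeces", which is an association and not a change over time.
- **Secondary objectives** includes "Evaluate changes in white blood cell RNA expression and DNA methylation profiles".
- The **primary objective** speaks generally of pharmacodynamic effects of seven days of metformin and names no outcome.
- **Study group** gives one alpha (0.05) and one power figure (at least 80%) without saying which outcome they concern.

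The text under Secondary parameters related to efficacy then says that statistically significant change will be the evidence for an effect on the microbiome, in composition and in function, and will confirm an effect on epigenetic regulation.

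**The concern.** A protocol should leave no doubt about which outcome is primary. Here a reader who starts from the efficacy parameters finds three primary families, and one who starts from the endpoints finds one. Methylation with transcriptome is primary in one section and secondary in two others. Change in microbiome function is primary in one section and is no endpoint in the other.

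What is at stake is the standing of the headline result. If the two lists remain, a finding in methylation, expression or function could be reported as primary by citing one section, and a null finding could be set aside as secondary by citing the other, after the data are known. The wording on significance adds to this, because it supports conclusions from each family whatever its rank. The primary endpoint also refers only to the time after metformin administration, and either of the two post-dose stool samples fits that description.

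**Working it through.** **Step 1. Set the sections side by side.**

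| Outcome family | Primary parameters for efficacy measurements | Endpoints of the study | Secondary objectives |
|---|---|---|---|
| Microbiome composition | Primary (item 1) | Primary, the only one | Appears through tolerance and diet questions; the change itself is not ranked |
| Microbiome function (gene families, pathways, metabolites) | Primary (item 2) | No endpoint for change; metabolites only in a taxon-metabolite association | Metabolites only in an association with composition |
| DNA methylation and RNA expression | Primary (item 3) | Secondary (endpoint 1) | Secondary (objective 3) |

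Only the first row is compatible across the sections. Endpoints of the study and Secondary objectives agree against the efficacy parameters on the third row. On the second row, nothing outside the efficacy parameters makes change in function a primary outcome.

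**Step 2. Look for a passage that decides.** The primary objective is too general to choose between the lists. The Project Summary ranks nothing. Study group ties its alpha and power to no outcome.

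**Step 3. Check the plan's own figure.** The inputs in Study group are 50 enrolled, about 2% loss, power of at least 80% and alpha 0.05. The loss step is consistent: 50 × (1 − 0.02) = 49 evaluable, and 49 / 0.98 = 50. The rest cannot be reproduced, because no effect size, standard deviation, test or outcome is given. The sample size therefore cannot show which outcome was meant as primary.

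**Step 4. Illustrate the size.** The assumptions are mine, not the protocol's: one test per family, each at 0.05, with significance in any one counting as success.

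- One primary outcome: 0.05.
- Three list items, independent: 1 − (1 − 0.05)³ = 1 − 0.857 = 0.143. Upper bound under any dependence: 3 × 0.05 = 0.15.
- Four, if methylation and transcriptome are counted apart: 1 − 0.95⁴ = 0.185. Upper bound: 4 × 0.05 = 0.20.

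Each family is itself high-dimensional, so one test per family is a simplification and not an account of the analysis under Methodology for data statistical analysis.

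**The case against.** The best defence is that parameters and endpoints do different jobs. The efficacy-parameter lists sort measurements, with direct changes called primary and associations called secondary. Only Endpoints of the study sets a hierarchy of hypotheses, and it names one primary endpoint. The study also calls itself exploratory.

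Part of this stands. The grouping is a possible reading, and the exploratory label lowers the consequence. It does not remove the contradiction. Both lists use the word primary, the protocol nowhere explains a difference in meaning, and methylation with expression is given opposite ranks.

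Four stronger readings are tempting, but the document does not support them.

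- *Three primary outcomes share a single 0.05.* Alpha appears only in the sample-size paragraph. Nothing says that it is shared, split or assigned to a family.
- *The study could be called positive on whichever family moves.* There is no study-level success rule. Each statement on significance is tied to its own domain: stool results to the microbiome, blood results to epigenetic regulation.
- *The tests are unadjusted.* The protocol does not say so, and a multiplicity procedure may sit in a statistical analysis plan that is not shown.
- *There are six chances of a false primary claim (three families at two post-dose times).* This gives 1 − 0.95⁶ = 0.265 under independence, with a bound of 6 × 0.05 = 0.30. It brings in the separate question of timing. Independence is also implausible, since both post-dose comparisons in a family use the same pre-dose sample. Any matching loss of power would rest on an effect size back-solved from a power statement that names no outcome.

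It is also too strong to say that function vanishes entirely from the endpoints, because metabolites remain in an association endpoint. What is missing is an endpoint for change in function.

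**Conclusion.** The contradiction is established from the text and needs no assumption: three primary items in one section, one primary endpoint in another, opposite ranks for methylation and RNA expression, and no endpoint for change in microbiome function. An unseen analysis plan could not make these two protocol sections agree.

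The false-positive figure of about 14%, with a ceiling of 15%, shows why the count matters. It holds only under the assumed rule of one test per family with any one sufficing, so it should not be quoted as the trial's error rate. In a study described as exploratory this should be corrected but does not undermine the design. The correction fixes what may be claimed as the primary result.

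**What to change.** Reconcile the lists in the direction that Endpoints of the study already takes, and that Secondary objectives supports for methylation and expression.

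1. Keep gut microbiome composition as the sole primary outcome.
2. Under Primary parameters for efficacy measurements, move items 2 and 3 to the secondary parameters.
3. Under Endpoints of the study, add change in microbiome function to the secondary endpoints.
4. Name the post-dose stool sample that carries the primary comparison. The sample at the end of the seven-day treatment (Day 11) against the pre-dose sample fits the primary objective; the early post-dose comparison would then be secondary.
5. Under Study group, state which outcome the power figure was calculated for. The sponsor should report what was actually done and not simply assert that it was composition, since the protocol does not show this.

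The cost is wording in three sections, with no change to samples, assays, visits or numbers enrolled. The downside is that methylation, transcriptome and function results are reported as secondary; for methylation and expression, two sections already say so.
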